The secondary outcome measures are as follows:Skin condition of the hands: self-assessed using the following item: ‘How would you rate the current condition of your skin using a school grading scale?’ (1 = very good, 2 = good, 3 = satisfactory, 4 = sufficient, 5 = poor, 6 = very poor).Skin condition of the hands (clinical-assessed, OHSI [61, 62]): semi-quantitative scoring system for the clinical assessment of hand eczema. Range from 0 to 18. Higher values indicate a worse skin condition.Action control: assessed with a 9-item scale, adapted from Scholz et al. [63]; items rated on a 7-point Likert scale (1 = does not apply at all, 4 = partly applies, 7 = applies exactly). A total score is calculated as the mean of all items (higher scores indicate greater action control). Items and scoring details are provided in Additional file 2.HRQoL: assessed with the Dermatology Life Quality Index (DLQI) [64].Employment status and number of days of sickness-related absence from work (due to the skin condition) during the follow-up period. This self-reported outcome may be influenced by external factors and will be interpreted with appropriate caution. However, no relevant confounding that would impair the comparability between groups is anticipated.

Additionally, in the intervention group only, the following will be assessed:Impact of the MiA app on goal achievement, measured using two items scored on a four-point scale (1 = strongly agree, 2 = rather agree, 3 = rather disagree, 4 = strongly disagree). The items are presented in Additional file 3.Usage behaviour of the MiA app: assessed centrally via usage data collected in the web-based dashboard (so-called Cockpit) over the entire 6-month follow-up period. This includes daily values for tracking skin protection behaviour, daily values for the use of photographic documentation including the number of images (up to four), and related comments.

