## Assignment of interventions: allocation

### Sequence generation {16a}

Participants will be allocated to either the intervention or control group in clusters based on their admission date at the clinic, following a predetermined quasi-randomisation allocation scheme. The assignment to the intervention or control group is thus planned prior to the start of the study. This pragmatic approach is justified for several reasons: firstly, patients will participate in a 3-week inpatient maintenance programme. Given the duration of their stay and the potential for interpersonal interactions, it is essential to incorporate designated wash-out periods to prevent contamination between groups. Additionally, participants will be allocated in clusters rather than at the individual level. Therefore, to ensure the study is completed within an appropriate timeframe, no alternative method of random group allocation is feasible. Furthermore, to minimise potential confounding due to seasonal factors and occupational patterns, the allocation scheme ensures that participants in both groups are recruited continuously throughout the entire year. This is important because climatic influences (such as winter cold) and the seasonal admission of certain occupational groups (e.g. construction workers more often admitted in winter) may affect outcomes; thus, both groups are exposed to these factors equally.

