## Data collection and management

### Plans for assessment and collection of outcomes {18a}

All data will be collected using paper-based forms. With the exception of the OHSI [61, 62], which is a physician-administered clinical assessment tool for evaluating the severity of hand eczema, all other data will be self-reported by study participants. At baseline, the following sociodemographic data will be collected: age, sex, current occupation, highest educational qualification, employment status, and relationship status. E-Health literacy in the context of medical app usage will also be assessed using the eHealth Literacy and Use Scale (eHLUS) [65]. In addition, primary and secondary outcomes will be assessed at baseline (see ‘Outcomes {12}’). The German-language data collection forms are available from the corresponding author upon request.

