A key advantage of LMMs is their robustness to missing data, which are common in longitudinal studies. Furthermore, LMMs allow the estimation of covariance structures even in studies with relatively small sample sizes, thereby improving the reliability of the results. All analyses will be conducted according to the intention-to-treat (ITT) principle, meaning that all randomised participants will be analysed in the groups to which they were originally assigned, regardless of their level of adherence to the intervention. This approach ensures that the effect estimates reflect the effectiveness of the intervention under real-world conditions. We acknowledge that variation in app usage in the intervention arm may attenuate the observed ITT effect; therefore, app usage will be summarised descriptively, and a pre-specified per-protocol sensitivity analysis will be conducted to assess robustness. To assess the robustness of the results, additional sensitivity analyses will be conducted, including a per-protocol (PP) analysis, which will consider only those participants who adhered to the study protocol as specified. This will include participants who complete all required assessments and, in the intervention group, use the app as specified. Comparing the results of ITT and PP analyses will enable for a more comprehensive evaluation of the stability and reliability of the findings. The significance level is set at *p* = 0.05. An overview of the intended analysis strategies is presented in Table 2.

**Table 2 Tab2:** Overview of planned statistical methods

Category	Outcome	Statistical analyses methods
Primary	Skin protection behaviour	• Statistical model: linear mixed model (LMM) (change t1 to t4)
Secondary	Skin condition of the hands (self-assessed; school grades: ordinal)	• Descriptive: mean value per group and time point • Statistical model: generalised linear mixed model (GLMM)
Secondary	Action control	• Descriptive statistics: mean and standard deviation per group and measurement time • Statistical model: LMM
Secondary	Health-related quality of life	• Statistical model: LMM
Secondary	Employment status	• Descriptive; two-sample *t*-test
Secondary	Sick days due to skin condition	• Descriptive; two-sample *t*-test
Further (intervention group only)	MiA app impact on goal achievement	• Descriptive

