#### Quasi-randomisation

In this trial, allocation to the intervention and control groups is conducted in clusters based on the date of admission to the clinic. This constitutes a pragmatic, quasi-randomised approach rather than strict randomisation and, as such, carries a risk of bias. In particular, confounding may influence any observed effects (i.e. differences in outcomes could be attributable to factors other than the intervention) [86]. Moreover, quasi-randomisation and the absence of allocation concealment render the study susceptible to allocation and selection bias. Knowledge of forthcoming group assignment may lead to systematic differences between groups and, in turn, affect study outcomes [86, 89]. Accordingly, we plan adjustment analyses (e.g. in the event of baseline imbalances) and will conduct sensitivity analyses to test the robustness of the results.

Notwithstanding these limitations, the chosen allocation method is a pragmatic alternative that enables the generation of decision-relevant evidence for the care of patients with WRHE. Quasi-experimental designs are well suited to producing causal inferences that are applicable to real-world implementation [90]. This is particularly pertinent here, as the TIP inpatient rehabilitation programme operates within relatively fixed parameters (treatment, patient education and counselling workflows) that align more naturally with a pragmatic study design than with an artificial experimental setting—an approach that could otherwise threaten external validity. In addition to the planned adjustment and sensitivity analyses, we will report the study in accordance with the updated guideline for reporting randomised trials (CONSORT 2025 Statement [91]) with particular attention to the CONSORT extension for cluster trials [92].

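### The protocol denies relevant confounding for skin-related sick days, against its own account of the allocation, and gives that outcome an unadjusted t-test with no adjustment tied to it

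*Protocol article*

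**What the plan says.** Outcomes {12} lists employment status and days of skin-related absence during follow-up as a secondary outcome. It first cautions: "This self-reported outcome may be influenced by external factors and will be interpreted with appropriate caution". It then adds that "no relevant confounding that would impair the comparability between groups is anticipated".

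The Quasi-randomisation part of the limitations takes the opposite line about the same allocation: "In particular, confounding may influence any observed effects". It adds that the lack of concealment leaves the study open to allocation and selection bias. It announces adjustment analyses, with baseline imbalance as the example, and sensitivity analyses.

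Sequence generation {16a} says that "the seasonal admission of certain occupational groups (e.g. construction workers more often admitted in winter) may affect outcomes", and argues that the allocation scheme exposes both groups to such factors equally.

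Table 2 in the statistical methods section {20a} reads: "Sick days due to skin condition • Descriptive; two-sample *t*-test". No covariate is named. The data collection section {18a} lists current occupation and employment status among the baseline variables, and says that "primary and secondary outcomes will be assessed at baseline".

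**The concern.** Absence from work because of a skin condition plausibly depends on the job. The protocol itself says that the occupational mix varies with admission time, and admission time determines the arm. The reassurance about confounding is thus attached to the outcome for which it is hardest to defend.

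If the arms differ in occupation, in employment status or in who agrees to take part, an unadjusted difference in mean sick days contains that difference as well as any effect of the intervention. A reader relying on the Outcomes section would be led to set that explanation aside. Work absence is an outcome that a statutory accident insurer, the funder here, is likely to read closely.

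**Working it through.** **1. The passages side by side.** The Outcomes sentence anticipates no relevant confounding for these two outcomes. The Quasi-randomisation section says that any observed effect may be confounded, and any effect includes one on sick days. The two statements cannot both stand unqualified.

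**2. Does the allocation scheme settle it?** Recruitment {15} describes alternating single-arm phases separated by 3-week wash-outs, so only one arm is recruited at a time. The window from May 13, 2025 to about October 2, 2026 is 507 days, or 507/30.44 = 16.7 months. It contains one winter, the season in which construction workers are said to be admitted more often. Balance on job mix then depends on how the phases fall across that winter. Alternation does nothing about selection at consent, since the concealment section {16b} says that patients learn their arm before consenting.

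**3. Does the announced adjustment settle it?** It names neither an outcome nor a covariate. Table 2, the outcome-specific plan, shows none for sick days. The only sensitivity analysis named in section {20c} is per-protocol. Section {20b} says that no additional analyses are planned.

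**4. Completers per arm.** The plan's sample size was reproduced first: d = 0.4, two-sided 5%, power 0.80, t-test with noncentral t. This gives 100 per arm (power 0.804), 200 in total, and 200/0.70 = 285.7, rounded up to 286 as stated. The sample size is not in question. The figure carried forward is 100 completers per arm.

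**5. Illustration of the bias.** The documents give no SD, imbalance or occupational gap for sick days, so the inputs below are assumptions.

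- Bias in SD units: b = (difference between arms in the share of a high-absence group) × (gap in mean days between that group and the rest, in SD).
- Rejection rate with no true effect: P(|T| > t critical), where T is noncentral t with 198 degrees of freedom and noncentrality b × √(100/2) = 7.07b.

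| Share difference | Gap (SD) | b (SD) | Noncentrality | Rejection rate |
|---|---|---|---|---|
| 5 points | 0.3 | 0.015 | 0.11 | 5.1% |
| 10 points | 0.5 | 0.05 | 0.35 | 6.4% |
| 20 points | 0.5 | 0.10 | 0.71 | 10.8% |
| 30 points | 0.5 | 0.15 | 1.06 | 18.4% |

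The rates apply only if the imbalance is systematic. Adjusting for the responsible covariate would bring the rate back to about 5%, provided the covariate is measured and the model is right.

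**The case against.** The strongest reply is that the protocol already deals with this. It urges caution about the outcome in the sentence just before the disputed one, offers a design argument for seasonal balance, and announces adjustment and sensitivity analyses. Covariates for each outcome are commonly left to the analysis plan, which is not shown. All of this softens the point. It does not remove the conflict between the two sections, nor the fact that the protocol itself fixes an unadjusted test for this outcome. Adjustment that depends on observed imbalance is also discretionary, and the Lack of blinding section says that the analyst recruits participants and conducts goal-setting interviews. An independent statistician's review is planned, but only at study completion.

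A second reply is that chance imbalance is already inside the nominal 5%. At 100 per arm and a prevalence of 30% to 50%, the standard error of a share difference is √(2 × 0.3 × 0.7/100) = 6.5 points to √(2 × 0.5 × 0.5/100) = 7.1 points, so 10 points is about 1.4 to 1.5 standard errors. This is fair for independent allocation of individuals, and it is why the rates above are conditional on a systematic difference. Here whole admission periods are allocated, so the reply holds only in part.

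Some stronger readings are tempting but not supported:

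- A reader might infer that the t-test was chosen because no confounding is anticipated. The two statements stand in separate sections, and Table 2 gives no reason for its test.
- A reader might infer that the protocol expects confounding. It says only that confounding may occur.
- A reader might infer that a baseline absence count is available. Sick days are defined over follow-up, and only the general sentence in {18a} implies a baseline value. Table 1, which might settle this, is not reproduced.
- A reader might infer that baseline variables are barred from every analysis of sick days. The announced adjustment excludes no outcome; it just is not tied to this one.

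**Conclusion.** The point holds in a limited form. The Outcomes sentence contradicts the Quasi-randomisation section and sits badly with the remark on seasonal job mix. Table 2 plans an unadjusted comparison of sick days, and the announced adjustment is not bound to it. The estimate can therefore carry differences in job mix or selection between arms.

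Neither the size nor the direction of any bias can be determined from the documents. An inflation of the 5% error rate to about 6% to 18% rests on an assumed systematic bias of 0.05 to 0.15 SD and 100 completers per arm; with smaller imbalances it is negligible. The point concerns a self-reported secondary outcome and leaves the primary analysis untouched. It should still be corrected, because the correction is cheap and relies on variables that the protocol says are collected.

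**What to change.** 1. In Outcomes {12}, delete the sentence on confounding, or qualify it so that it agrees with the Quasi-randomisation section.
2. In Table 2, replace the t-test for sick days with a prespecified regression, for example linear with robust standard errors or a count model. Its terms are arm, baseline occupational group and baseline employment status, plus prior skin-related absence if it is collected. Define the occupational groups in advance, and fit the model whatever imbalance is observed.
3. Report the unadjusted difference beside the adjusted one.

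The cost is one sentence, one table row and slightly more analysis work. No additional patients are needed, nor any new data for the two core covariates. Recruitment was due to run to about October 2026, so the change can be made before analysis. Adjustment will not remove selection on unmeasured factors, and the report should say so.

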### Participant timeline {13}

The participant timeline of enrolment, allocation, interventions, and assessments is presented in Table 1.

**Table 1 Tab1:**
[figure not shown]
Participant timeline of enrolment, allocation, interventions, and assessments

Abbreviations: *DLQI* Dermatology Life Quality Index, *eHLUS *eHealth Literacy and Use Scale, *HRQoL *health-related quality of life, *MiA app *German acronym for ‘Mein Hautschutz im Alltag’, English ‘My Skin Protection in Everyday Life’, *OHSI* Osnabrück Hand Eczema Severity Index

### Sample size {14}

The anticipated primary outcome of the study is the improved skin protection behaviour of participants. The following assumptions and calculations form the basis for determining the total sample size: the sample size was planned a priori based on a *t*-test for independent samples, comparing the change scores (difference between t1 and t4) between the intervention and control groups. A mean effect size of *d* = 0.4 was assumed to determine the required sample size. This anticipated effect is expected to lie in the lower range between small and medium. With a significance level of *α* = 0.05 (two-tailed), a statistical power of 1 − *β* = 0.80, and an expected dropout rate of 30%, the required total sample size was calculated to be *N* = 286 participants. This total sample will be divided into the following groups: intervention group with *n* = 143 participants and control group with *n* = 143 participants. The dropout rate of 30% was based on literature reporting the effectiveness of app-based interventions for behaviour change [66, 67]. Previous studies have also indicated that the actual response rate in app-based interventions may, in some cases, exceed the projected dropout rate of 30%. The sample size calculation was conducted using G*Power software version 3.1.9.7 [68].

### Recruitment {15}

Participants in the TIP programme will be approached personally by researchers and invited to participate in the study (see item 26a). Recruitment will take place at the iDerm in Osnabrück, Germany, from May 13, 2025, until approximately October 2, 2026. Initially, only participants for the intervention group will be recruited. After a 3-week wash-out period, participants for the control group will be recruited. This procedure will then repeat: a recruitment phase for the intervention group will be followed by another 3-week wash-out phase, and then a recruitment phase for participants for the control group. The wash-out phases are needed to prevent contamination between the intervention and control groups. Throughout the recruitment phase, the recruitment status will be continuously monitored to ensure adherence to the study protocol.

## Assignment of interventions: allocation

### Sequence generation {16a}

Participants will be allocated to either the intervention or control group in clusters based on their admission date at the clinic, following a predetermined quasi-randomisation allocation scheme. The assignment to the intervention or control group is thus planned prior to the start of the study. This pragmatic approach is justified for several reasons: firstly, patients will participate in a 3-week inpatient maintenance programme. Given the duration of their stay and the potential for interpersonal interactions, it is essential to incorporate designated wash-out periods to prevent contamination between groups. Additionally, participants will be allocated in clusters rather than at the individual level. Therefore, to ensure the study is completed within an appropriate timeframe, no alternative method of random group allocation is feasible. Furthermore, to minimise potential confounding due to seasonal factors and occupational patterns, the allocation scheme ensures that participants in both groups are recruited continuously throughout the entire year. This is important because climatic influences (such as winter cold) and the seasonal admission of certain occupational groups (e.g. construction workers more often admitted in winter) may affect outcomes; thus, both groups are exposed to these factors equally.

### Concealment mechanism {16b}

Concealment of group allocation from the researchers and recruiters is not feasible, since allocation is predetermined by the date of admission to the clinic. This limitation is inherent to the design of a quasi-randomised controlled trial, where allocation is based on factors such as the date of admission and cannot be concealed from the researchers or recruiters. Potential participants are informed of their assignment to either the intervention or control group prior to providing their written informed consent.

## Assignment of interventions: blinding

### Who will be blinded {17a}

The study participants will not be blinded, as their participation in the individual goal-setting interview and the use of the app will inherently preclude blinding. Additionally, the individual goal-setting interviews will be conducted by researchers, which will also prevent blinding.

### Procedure for unblinding if needed {17b}

This study is not blinded; therefore, there is no unblinding procedure.

## Data collection and management

### Plans for assessment and collection of outcomes {18a}

All data will be collected using paper-based forms. With the exception of the OHSI [61, 62], which is a physician-administered clinical assessment tool for evaluating the severity of hand eczema, all other data will be self-reported by study participants. At baseline, the following sociodemographic data will be collected: age, sex, current occupation, highest educational qualification, employment status, and relationship status. E-Health literacy in the context of medical app usage will also be assessed using the eHealth Literacy and Use Scale (eHLUS) [65]. In addition, primary and secondary outcomes will be assessed at baseline (see ‘Outcomes {12}’). The German-language data collection forms are available from the corresponding author upon request.

### Plans to promote participant retention and complete follow-up {18b}

Participants will receive information at the beginning of the study regarding the procedures and the scope of data collection. The importance of providing complete feedback will be explicitly emphasised. The questionnaires will be sent to study participants in both groups by post, accompanied by prepaid return envelopes. In the event of no response, participants will receive a postal reminder (including a questionnaire) after 2 weeks. To enhance motivation for participation, study participants in both the intervention and control groups who return all questionnaires fully completed and in a timely manner at the four assessment points will be entered into a prize draw. Forty gift vouchers, valued at €50.00 (including VAT), are available as prizes. Eligibility for the prize draw is not influenced by the content of the responses, but only by the timely and complete return of the questionnaires. Participants are informed of this during the recruitment process.

